### 2.4. Study Materials

While all surveys will be delivered using REDCap, we will use an additional six primary tools to deliver the ACTIVE intervention and obtain study data. These tools include (1.) Fitbit/Fitabase, (2.) myACTIVEsteps.com, (3.) printed educational materials, (4.) instructional education videos, (5.) physical therapy videos, and (6.) the Zoom video conferencing application.

Fitbit Inspire 3 Smartwatch and Fitabase: Participants will receive a pre-configured de-identified Fitbit Inspire 3 smartwatch to passively collect activity data, including daily step counts, activity intensity (daily duration of light, moderate, and intense physical activities), and daily heart rate variability. Fitabase, a secure HIPAA-compliant data management platform, will link each device to a study-specific dashboard and capture all transmitted Fitbit data in real time. Also, motivational text messages will be sent from the Fitabase platform to all study participants.

myACTIVEsteps.com Platform: This secure website houses all asynchronous video-guided physical rehabilitation sessions and instructional educational modules [34]. The website automatically captures engagement metrics, including logins, video access, and watch time (in minutes) for both the video-guided physical rehabilitation sessions and educational modules.

Printed Educational Materials: Care recipients and partners will receive printed copies of the Centers for Disease Control and Prevention’s fall prevention resources—“Stay Independent” [35], and “Family Caregivers: Protect Your Loved Ones from Falling” [36].

Instructional Educational Videos: Care recipients and care partners will access three-minute educational videos during the intervention period. The content of these videos was developed by the study team and is grounded in evidence-based fall prevention strategies from the Centers for Disease Control and Prevention (CDC) STEADI initiative [35,36,37]. Care recipient videos will focus on (1) benefits of moving, (2) safe home exercises, (3) fall prevention, (4) pain management, (5) building routines, and (6) long-term strength and independence. Care partners will receive parallel educational modules emphasizing (1) their role in supervision, (2) setting up safe environments, (3) recognizing risks, (4) encouraging safe activity, (5) reinforcing progress, and (6) transitioning support as independence improves.

Video-Guided Physical Rehabilitation videos: Care recipients and their care partners will have access to nine asynchronous evidence-based video-guided physical rehabilitation videos created by the National Institute on Aging (US), the Falls Prevention and Healthy Aging Network (Australia), and the National Health Service Inform Falls Information Zone (UK). Video content covers gait, strength, and balance training, and each video lasts 10 to 15 min. The study team obtained permission to use these publicly available videos.

Zoom Videoconferencing: Qualitative interviews will be conducted via Zoom, using audio-only recording. Recordings will be transcribed using a secure AI-assisted transcription service, and transcripts will be de-identified before analysis.

Study materials and surveys are available in both English and Spanish. Bilingual staff will conduct interviews and provide support for Spanish-speaking dyads. Expert physical therapy educational videos are delivered in English, and Spanish subtitles will be available for Spanish-speaking participants. All participant-facing materials, including surveys, consents, videos, and platform content translated from English to Spanish, will be validated by bilingual experts prior to use.

### 2.5. Intervention Design

The ACTIVE intervention consists of six co-occurring events as follows (Table 1):

Activity Tracking: Care recipients and their care partners will be provided with a wrist-worn Fitbit smartwatch to wear during waking hours for at least 8 h per day. Activity metrics will be tracked for care recipients and care partners on Fitabase.

Care partner co-participation: Care partners will play active, structured roles in the intervention. These roles include (1.) Safety oversight, (2.) Co-engagement, (3.) Education access and (4.) Motivation and supervision. Care partners will be required to ensure their care recipients use the smartwatch consistently, walk safely, and adhere to exercise protocols (safety oversight). They will participate in walking exercises and video-guided physical rehabilitation sessions together with their care recipient (co-participation). They will view educational videos to understand how best to support care recipients to stay active in safe environments (education). Lastly, they will encourage adherence, monitor fatigue, and help adjust routines as independence improves (motivation and supervision). Care partner engagement will be assessed using a multimodal approach, including platform-based analytics (login frequency, module completion), structured prompts embedded within myACTIVEsteps, and brief scheduled daily text message check-ins to capture real-time participation and support activities.

Text reminders: Validated motivational text messages will be delivered to both care recipients and care partners at scheduled morning times tailored to each dyad. These messages were developed using Self-Determination Theory. They encompass nine activity-based categories: (1) exceeding the daily activity goal; (2) meeting the daily target; (3) slightly below target; (4) low activity; (5) no activity data received; (6) improvement in activity compared with the prior day; (7) decrease in activity compared with the prior day; (8) three or more consecutive days of high activity; and (9) three or more consecutive days of low activity. Details of the development and validation of the motivated text messages have been published [38]. Message delivery will be dynamically tailored based on each participant’s recorded activity from the preceding day (e.g., exceeded goal, low activity, no data, or sustained inactivity). Messages will be brief, supportive, and action-oriented, serving as daily prompts to reinforce engagement and sustained physical activity.

Instructional education: Care recipients and care partners will be assigned six brief instructional videos (2–3 min each), organized into twice-weekly educational modules delivered over the three-week intervention period. Video engagement will be automatically tracked through the myACTIVEsteps platform. A video will be considered completed if at least 70% of the total viewing time is reached.

Virtual physical therapy: Care recipients and their care partners will have access to nine evidence-based video-guided physical rehabilitation modules over three weeks—three videos per week, each lasting 10–15 min. Duration of engagement and percent completion will be tracked remotely on the website. A video session will be considered completed if at least 70% of the total viewing time is reached. We expect both care partners and their care recipients to participate in each session. At the start of each session, the user ID of the person logging in will be required, and the person will attest that the care partner/care recipient is available during the session.

Exercise (Walking Program): The walking program emphasizes daily walking, ideally outdoors or in safe indoor settings (hallways, local community centers, schools, malls, walking paths). Care recipients will be encouraged to walk with their care partner at least once daily, starting with 10–15 min and gradually increasing to 30 min per day, 5 days a week. Care partners will monitor pacing, ensure environmental safety, and help reinforce adherence. Walking activity will be tracked by the smartwatch and reinforced through motivational texts.

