Dyads that consent will complete a self-administered baseline survey (discussed below). Also, during the video call, the study team will guide the care recipient and care partner in creating user accounts on myACTIVEsteps.com and Fitabase, and on the Fitbit smartwatch (discussed below), using their preferred names, user identities (IDs), and phone numbers. Each video enrollment session is expected to last between 45 and 60 min. After the video call, the study materials (Fitbit smartwatch, educational materials on fall prevention, and instructions for accessing the online videos and using the smartwatch) will be sent to study participants within 1 week of enrollment. All surveys and consents will be administered remotely on Research Electronic Data Capture (REDCap) [33]. All study participants will be informed that de-identified ACTIVE study data may be used for future ancillary studies without additional participant contact, subject to IRB approval.

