### 2.13. Analysis Plan

Handling of Missing Data: We anticipate low levels of missing data, which will be assessed for randomness using Little’s test [63,64]. Multiple imputation with chained equations will be used when appropriate [65,66,67], with sensitivity analyses to evaluate robustness of results. For feasibility outcomes, missing data will be minimized through proactive monitoring and participant reminders, and patterns will be summarized descriptively. For preliminary efficacy analyses, linear mixed-effects models will accommodate incomplete longitudinal data under an intention-to-treat framework. The percent and potential impact of missing data will be reported.

Feasibility Assessment: Six feasibility outcomes (recruitment, adoption, adherence, acceptability, fidelity, retention): will be summarized overall and stratified by AD/ADRD status (dyads with mild AD/ADRD and dyads without mild AD/ADRD) and by participant role within the dyad (care recipient vs. care partner). We will report the proportions and mean distributions, including 95% confidence intervals, for the feasibility measures, and descriptively compare these values with the preset benchmark (Table 3). A “go” decision will be made if the majority of benchmarks are met, a “conditional go” if some but not all benchmarks are achieved (with justification for modifications), and a “stop” decision if most benchmarks are not met. Feasibility outcomes will be assessed separately by AD/ADRD status and by intervention and control arms. Differences in feasibility outcomes by AD/ADRD status and by participant role will be explored descriptively using mean differences and differences in proportions with 95% confidence intervals.

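### Recorded completion of a rehabilitation video does not show that the care recipient took part, so the comparison by role on the rehabilitation items cannot be interpreted

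*Protocol article*

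**What the plan says.** **Completion rule.** Section 2.5 (virtual physical therapy): "A video session will be considered completed if at least 70% of the total viewing time is reached".

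**Identification.** The same paragraph sets the check made when a session opens: "the user ID of the person logging in will be required, and the person will attest that the care partner/care recipient is available". The sentence goes on to make clear that the availability attested to is for the session itself. Joint participation is stated as an expectation: "We expect both care partners and their care recipients to participate in each session".

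**What the platform records.** Section 2.4 lists logins, video access and watch time. Section 2.2 has the study team "guide the care recipient and care partner in creating user accounts on myACTIVEsteps.com and Fitabase", so both members hold accounts.

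**Further checks.** For care partner engagement, Section 2.5 adds platform analytics, prompts on the site and "brief scheduled daily text message check-ins to capture real-time participation and support activities". No equivalent is stated for care recipients, and none of these checks enters the completion rule.

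**Use of the measure.** Section 2.10 and Table 3 make completed rehabilitation sessions one of three adherence indicators, with a 75% target. Table 3 also has an adoption item of at least one rehabilitation session. Section 2.13 summarises all six feasibility outcomes by role and explores role differences with 95% confidence intervals. Section 2.8 uses rehabilitation completion as its worked example of precision, with 100 individuals in 50 dyads and an ICC of 0.2.

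**The concern.** The analysis calls for a measure on each person. The completion rule yields viewing time under one named user, plus that user's statement that the other member is available. Being available is weaker than taking part, and watch time shows that a video played, not that anyone exercised.

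The article does not say to whom a completed session is credited. Under either obvious rule, the contrast between care recipient and care partner on this item says nothing about how the two members behaved. The recorded figure can also overstate participation by the care recipient, who is the main target of the rehabilitation. An analysis plan written later could choose a crediting rule, but it could not recover participation that was never recorded.

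**Working it through.** **Inputs from Section 2.8:** p = 0.75, n = 100 individuals, cluster size m = 2, ICC = 0.2. **Assumed, because the article gives no values:** q, the share of sessions completed; s, the share of completed sessions in which the recipient logs in; r, the share of partner-logged sessions in which the recipient truly takes part.

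**1. The plan's own figure reproduces.**
- Unadjusted SE = √(0.75 × 0.25 / 100) = 0.0433.
- Design effect = 1 + (2 − 1) × 0.2 = 1.2.
- Adjusted SE = 0.0433 × √1.2 = 0.0474.
- 95% CI = 0.75 ± 1.96 × 0.0474 = 0.657 to 0.843, which matches the stated 0.66–0.84.

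**2. Both members credited for each session.** The two members then have the same record, so the role difference is exactly 0 whatever they did, and the ICC for this item is 1.
- Design effect = 1 + (2 − 1) × 1 = 2, so the effective sample size is 100 / 2 = 50.
- SE = 0.0433 × √2 = 0.0612.
- 95% CI = 0.75 ± 1.96 × 0.0612 = 0.63 to 0.87.
- Within one AD/ADRD stratum (25 dyads, 50 people), the interval is 0.58 to 0.92 with SE 0.0866, against 0.62 to 0.88 with SE 0.0671 at ICC 0.2.

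The recorded rate for the recipient can also differ from true participation. If the recipient takes part in every session that he or she logs in to, true participation = q × [s + (1 − s) × r]. With a recorded rate of q = 0.75:

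| s | r | True recipient participation |
|---|---|---|
| 0.2 | 0.5 | 0.45 |
| 0.2 | 0.75 | 0.60 |
| 0.5 | 0.5 | 0.56 |
| 0.5 | 0.75 | 0.66 |
| any | 1 | 0.75 |

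**3. Only the person logging in credited, with one login per session.** Suppose both members truly take part in every completed session. Recorded recipient rate = q × s, recorded partner rate = q × (1 − s), and difference = q × (2s − 1). With q = 0.75:

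| s | Recipient | Partner | Recorded difference | True difference |
|---|---|---|---|---|
| 0.2 | 0.15 | 0.60 | −0.45 | 0 |
| 0.5 | 0.375 | 0.375 | 0 | 0 |
| 0.8 | 0.60 | 0.15 | +0.45 | 0 |

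The recorded difference follows login habits alone.

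**The case against.** Several counter-arguments carry weight.

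- **Scope.** A reader might infer that care-recipient adherence as a whole, and the whole comparison by role, depend on who logs in. The article does not support that. Smartwatch days come from a watch that each member wears. Educational videos are parallel modules for each role. Neither uses the shared-session attestation. Only the two rehabilitation items are affected.
- **Crediting.** A reader might also infer that both roles can never reach 75%. That needs exactly one login per session and credit to that person alone, and the article states neither. Both members have accounts, and separate logins are not excluded. Crediting both members fits the attestation better, so the large differences in step 3 belong to the less plausible rule.
- **Decision rule.** The 75% benchmark is not stated as applying to each role separately. The go decision depends on the majority of benchmarks, and role differences are descriptive only.
- **Other checks.** Care-partner prompts and daily texts, and the weekly dyad telephone check-ins in Table 2, may give some information on joint participation. The Discussion also plans to cross-check self-report against platform data where possible. But none of this is tied to completion of a session, and platform data cannot show exercise by the member who is not logged in.
- **Condensed article.** The crediting rule could reasonably sit in a fuller document. The missing rule alone would not be a finding. What remains is that the measure as stated holds no record of participation by each member for a later rule to work on.

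A descriptive comparison must still measure what it names, so the narrower point stands.

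**Conclusion.** The point holds for the rehabilitation adherence item and the rehabilitation adoption item only. Recorded completion does not establish that the care recipient took part, and the planned comparison by role on these items has no useful interpretation under either crediting rule.

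If both members are credited, the half-width of the 95% CI at 75% completion rises from about 0.09 to 0.12 (0.63–0.87 in place of 0.66–0.84). This follows from identical records and needs no assumption about behaviour. The gap between recorded and true recipient participation, and the role differences under logger-only credit, rest on assumed values of s and r and show only what is possible. The article gives no basis for saying that care partners will in fact do most of the logging in, or that the go decision would change. This is an inexpensive improvement to one measure and does not undermine the feasibility assessment as a whole.

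**What to change.** 1. Add a prompt on myACTIVEsteps at the end of each rehabilitation video, once the 70% mark has been reached, with two yes/no items: the care recipient did the exercises; the care partner did the exercises.
2. Credit each member from these answers, and keep the login ID as descriptive information only.
3. Report completion confirmed for the care recipient, and joint completion, alongside the existing 70% viewing-time measure. State in Sections 2.5 and 2.10 and in Table 3 which of these each figure uses.
4. If confirmation for each member is not collected, treat rehabilitation completion as a dyad-level outcome (n = 50), state its precision on that basis, and drop the comparison by role for the two rehabilitation items.

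The cost is two tick boxes on a site that is already planned to carry prompts, plus a few lines of text. The confirmation remains self-reported, or proxy-reported when one member answers for both, so it improves on availability attested at the start but does not verify participation. Stated adherence may be lower than under viewing time alone.

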### 2.6. Intervention and Control Groups

Dyad participants randomized to the intervention arm will experience all six components of the ACTIVE intervention—Activity tracking, Care partner co-participation, Text reminders, Instructional education, Video-Guided Physical Rehabilitation, and Exercise. Dyad participants randomized to the control group will receive the Fitbit smartwatch only for physical activity tracking. They will be instructed to wear the smartwatch daily during waking hours. They will not receive motivational text messages, instructional education, or video-guided physical rehabilitation content during the intervention period. Dyad participants in the intervention and control arms may choose to discontinue participation at their own request without penalty. If either member of a dyad chooses to discontinue participation, the entire dyad will be withdrawn from the study. Participants will also be encouraged to continue their regular healthcare and daily routines.

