### 2.8. Sample Size Determination

For this pilot study, the trial is not powered to detect clinical efficacy but to provide adequate precision for estimating feasibility metrics and to inform the design of a future fully powered effectiveness–implementation trial [44]. We will enroll 50 dyads (older adult + care partner), a recommended sample size for behavioral pilot trials and digitally delivered rehabilitation interventions [44,45,46]. A sample of 50 dyads (n = 100) provides adequate precision to estimate key feasibility parameters that guide go/no-go decisions.

For a feasibility outcome, the unadjusted standard error (SE), assuming independence, is estimated using the formula in Equation (1). Using an expected proportion of 0.75 (e.g., completion of ≥75% of virtual PT modules), the unadjusted SE is 0.043.(1)SE=p (1−p)n

To account for dyadic clustering, we assume an intra-cluster correlation (ICC) of 0.1–0.3, which is typical for partner dyads [47,48]. Using the design effect formula in Equation (2), an ICC of 0.2, and a cluster size (m) of 2, the design effect is 1.2, and the cluster-adjusted SE (Equation (3)) is 0.047. The cluster-adjusted 95% CI for a 75% completion rate (Equation (4)) is therefore 0.66–0.84.Design Effect = 1 + (m − 1) × ICC(2)Cluster-adjusted Standard Error (adjusted SE) = Unadjusted SE × √(Design Effect)(3)(4)95% CI=p±1.96×adjusted SE

This level of precision is appropriate for feasibility-focused pilot research, where the goal is to estimate plausible ranges and plan thresholds for an adequately powered future trial.

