### 2.9. Data Collection, Management, and Retention

Across the study period, we will collect (1) feasibility measures, (2) preliminary efficacy measures, (3) covariates, and (4) qualitative interview data from older adults and their care partners (Table 3). Data will be captured through surveys, Fitbit/Fitabase activity monitoring, myACTIVEsteps.com engagement metrics, and Zoom-based interviews.

All data will be coded with unique study IDs and stored securely on access-restricted institutional servers, with access limited to authorized study personnel. No direct personal identifiers will be collected, and only de-identified data will be shared for analysis or future research. Data integrity will be maintained through standardized collection protocols, regular quality checks, and audit trails. Study data will be retained in accordance with institutional and federal requirements.

Participant retention will be promoted through proactive monitoring, reminders, and flexible follow-up scheduling. Even in cases of partial discontinuation, key outcomes will be collected when possible, including remote data capture for surveys and activity tracking.

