where *Y_idt_* = outcome, *β*_0_ = fixed intercept, *Trt_i_* = treatment indicator, *Seq_i_* = sequence indicator, *Y_id_*_0_ = baseline value of the outcome, *Demi* = dementia status, *Trt × Dem* = treatment-by-dementia interaction, *Trt × Period =* treatment-by-crossover interaction, γ^⊤^*X_i_* = coefficient of covariates, and *b_d_* and *b_i(d)_* are the random intercept for dyad and individual nested within dyad, respectively. Treatment condition (intervention vs. control) and sequence (intervention-first vs. intervention-second) will be included as fixed effects to estimate the average intervention effect and to account for between-participant differences related to assignment order, respectively. Time will be modeled as a continuous weekly measure to capture trends over the six-week follow-up. Period will be modeled separately as a categorical indicator of pre- versus post-crossover phase to distinguish underlying activity trajectories from changes associated with withdrawal of active intervention components. Given the anticipated persistence of learning effects due to the short one-week washout period, the treatment × period interaction will be used to characterize maintenance or attenuation of intervention effects rather than to assume their absence. All analytical models will follow the intention-to-treat principle, and effect sizes with 95% confidence intervals will be reported to inform power calculations for a future definitive trial.

Qualitative Assessment: Semi-structured interviews will be conducted with dyads after completing the intervention phases. Dyads initially randomized to the intervention arm will be interviewed at crossover, while those starting in the control arm will be interviewed after completing the delayed intervention. Interviews will explore barriers and facilitators to smartwatch use, motivational texts, instructional educational modules, engaging in video-guided physical rehabilitation, walking exercise, and co-participating with a care partner. While we estimate conducting 10 to 20 interviews each for those with and without mild AD/ADRD, the exact number will be guided by the achievement of thematic saturation [68,69].

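### Withdrawing the whole dyad when one member stops does not separate ending the intervention from ending data collection, and creates avoidable missing data for a willing randomised member

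*Protocol article*

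**What the plan says.** Section 2.6 (Intervention and Control Groups) sets the withdrawal rule for both arms: "If either member of a dyad chooses to discontinue participation, the entire dyad will be withdrawn from the study". It draws no line between giving up the joint intervention and ending data collection.

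Section 2.9 (Data Collection, Management, and Retention) makes a commitment in the other direction: "Even in cases of partial discontinuation, key outcomes will be collected when possible, including remote data capture for surveys and activity tracking". It does not define partial discontinuation.

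Section 2.13 (Analysis Plan) says that "linear mixed-effects models will accommodate incomplete longitudinal data under an intention-to-treat framework", and later that "All analytical models will follow the intention-to-treat principle". The model is written for individuals within dyads: its two random terms "are the random intercept for dyad and individual nested within dyad, respectively".

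Section 2.10 defines retention on dyads, with a benchmark of at least 75%. No section explains how the rule in 2.6 and the commitment in 2.9 fit together.

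**The concern.** When one member stops and the other is willing to go on, section 2.6 tells staff to withdraw both. Section 2.9, read naturally, tells them to keep collecting surveys and watch data. Staff cannot do both for the willing member.

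The rule turns one person's decision into missing outcomes for two. The pilot has 50 dyads, and its effect sizes are meant to feed the power calculation of a definitive trial.

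The survey outcomes are the most exposed. Each has a baseline value and few later assessments, and the baseline enters Equation 5 as a covariate. A dyad withdrawn before its first post-baseline survey therefore adds no observed survey outcome. Section 2.13 also promises feasibility results by role within the dyad, and the rule removes the remaining member's later adherence and acceptability data from that comparison.

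**Working it through.** **Inputs from the document.** 50 dyads, 100 people (2.8); expected proportion 0.75 (2.8); ICC 0.2 within a range of 0.1 to 0.3, cluster size 2 (2.8); retention benchmark 75% of dyads (2.10).

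**Assumptions, because the document gives no figure.** The probability q that a member chooses to stop, and the within-dyad correlation ρ of stopping, taken as 0 to 0.3. The ICC in 2.8 is for a feasibility proportion, so using values of that size for stopping is itself an assumption.

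**The plan's own figure.** Section 2.8 states: "Using an expected proportion of 0.75 (e.g., completion of ≥75% of virtual PT modules), the unadjusted SE is 0.043".
- Unadjusted SE = √(0.75 × 0.25 / 100) = 0.0433.
- Design effect = 1 + (2 − 1) × 0.2 = 1.2.
- Adjusted SE = 0.0433 × √1.2 = 0.0474.
- 95% CI = 0.75 ± 1.96 × 0.0474 = 0.657 to 0.843, half-width 0.093.

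This reproduces the stated 0.66 to 0.84. It assumes that all 100 people contribute. The figure is not in dispute.

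**Loss at the retention benchmark.** Let p = 1 − q be the probability that a member is willing to stay. Then P(both stay) = p² + ρp(1 − p). Setting this to 0.75 means 12.5 of 50 dyads, or 25 of 100 people, are withdrawn.

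| ρ | p | Chose to stop, 100(1 − p) | Willing but withdrawn | 25 / chose to stop |
|---|---|---|---|---|
| 0 | 0.866 | 13.4 | 11.6 | 1.87 |
| 0.2 | 0.851 | 14.9 | 10.1 | 1.68 |
| 0.3 | 0.843 | 15.7 | 9.3 | 1.59 |

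**Loss at other assumed rates.** Willing people withdrawn = 100 × [(1 − q) − P(both stay)]. Ranges run over ρ from 0 to 0.3.

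| q | Still in the study under 2.6 | Still followed if willing members stay | Willing but withdrawn |
|---|---|---|---|
| 10% | 81 to 84 | 90 | 6 to 9 |
| 15% | 72 to 76 | 85 | 9 to 13 |
| 20% | 64 to 69 | 80 | 11 to 16 |

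**Effect on precision** (proportion 0.75, ICC 0.2, ρ = 0). Under the dyad rule, SE = √(0.1875 × 1.2 / N), where N is the number still in the study. If willing members are followed, with k complete pairs and s single members, SE = √(0.1875 × (2k × 1.2 + s)) / (2k + s).
- q = 10%: N = 81 gives half-width 0.103. With 2k = 81 and s = 9 it is 0.097.
- q = 20%: N = 64 gives half-width 0.116. With 2k = 64 and s = 16 it is 0.102.

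These half-widths treat a withdrawn person as contributing nothing, so they are an upper bound for measures on which earlier data are kept.

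**Does the design need the rule?** The model has a random intercept for each individual within the dyad, so it can use one member's data alone. Retention is scored on dyads, so a dyad can count as not retained while one member is still followed. The control condition is the watch only, so shared exercise cannot be the reason to end tracking there.

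**The case against.** The other side has several sound points.

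- **Partial discontinuation has a softer reading.** It could mean someone who drops some components but stays enrolled, and the commitment in 2.9 applies only where collection is possible. On that reading 2.6 and 2.9 can both be followed. This stands as a possible reading, but it does not remove the avoidable loss of the willing member.
- **Intention-to-treat is not ruled out.** A reader might infer that 2.6 makes the promised analysis impossible. It does not: participants can still be analysed as randomised, and 2.13 provides for incomplete data in the mixed models, multiple imputation and sensitivity analyses.
- **Dropout related to arm or dementia status does not in itself bias the effect.** A reader might infer that heavier loss on the intervention or in AD/ADRD dyads must distort the pre-crossover estimate. Treatment, dementia status and their interaction are fixed effects in Equation 5, so dropout that depends only on them is missing at random given the model. The document also gives no figure showing that loss will differ in this way; section 3 says only that care partners' engagement may vary with burden and competing duties.
- **Nothing says earlier data are deleted.** The loss concerns what would have been collected after withdrawal.
- **The dyad is a reasoned unit.** Enrolment, randomisation and retention are dyadic, care partners give safety oversight, and a care partner may be the legally authorised representative. This supports ending the joint intervention together. It does not by itself require follow-up of a consenting person to end.
- **The precision cost is modest.** At 10% member discontinuation the half-width moves from 0.097 to 0.103, in a pilot with no power claim.

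**Conclusion.** The point holds as a question of consistency and avoidable missing data. Section 2.6 does not separate stopping the dyadic intervention from stopping data collection. It conflicts with 2.9 on the natural reading of partial discontinuation. On any reading it ends follow-up of a willing randomised member whose data the model could use, and so weakens the intention-to-treat analysis.

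The size rests on assumptions, because no dropout rate is stated and 75% is a minimum target, not a forecast. At exactly 75% dyad retention, with a correlation of 0 to 0.3, about 9 to 12 of the 25 people withdrawn would have been willing to continue. The total loss is then about 1.6 to 1.9 times the loss from those who chose to stop. Calling it a doubling is right only for a dyad in which one member stops alone.

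The main consequence is lost precision. Bias is possible if stopping depends on outcomes that are not observed, but the document does not show that it does. The point deserves a change to the text. It does not undermine the trial.

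**What to change.** Reconcile sections 2.6 and 2.9 by separating two events: the end of the dyadic intervention and the end of follow-up.

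- When one member stops, count the dyad as not retained for the 75% benchmark.
- Continue remote Fitbit and survey collection from each member whose own consent, or valid representative consent, remains in force.
- End data collection only for a person for whom no valid consent remains.
- State in 2.13 that all available data from randomised participants enter the models.
- Define partial discontinuation in 2.9 to match.

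This concerns data collection only; when the intervention itself should stop is left to the investigators.

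The cost is mainly protocol and consent wording, because collection is already remote. There is one real limit. If a care recipient lacks capacity and the departing partner was the consenting representative, collection must end for that care recipient when no valid consent remains. Some loss in the AD/ADRD stratum therefore cannot be avoided.
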